**Methods:**

A case-control study will be conducted on at least 100 patients diagnosed with IBD, matched with 100 healthy individual controls. The matching will include sex, age, and education. Patients will be fully examined, and a full interview and a neurological and cognitive examination will be performed. The primary clinical outcomes will be cognitive test scores (Montreal Cognitive Assessment, Trail Making Test, Digit Symbol Substitution Test, forward and backward digit span testing). Depression, stress, and anxiety screening will also be performed. Blood samples from all participants will be collected, and aliquots will be immediately stored in a biobank. Primary laboratory outcomes will include serum levels of presumed cognitive dysfunction blood biomarkers SAA, Hcy, S100B, and BDNF. Follow-up will be performed at 12, 24, 36, and 48 months.

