### Sites, Population, and Case and Control Definitions

The study will take place in Cluj-Napoca, Romania, in the Clinical CF Hospital and the Regional Institute for Gastroenterology and Hepatology “Octavian Fodor.” An agreement was obtained from all the participant clinics.

Two separate groups consisting of at least 100 patients with IBD and at least 100 HC will be recruited. The study will be carried out from May 2021 to January 2030. The HC will be matched with the patients with IBD based on age, sex, and education.

Patients included in the case (IBD) group need to have a clear diagnosis of IBD. For this, a histopathological examination proof will be obtained from the databases of the participant centers or from the personal records of the patients (if the site does not have the original proof diagnosis).

The HC will be recruited from the day care hospital and ambulatory. Their diagnosis must have never been IBD, and they should be in good health at the moment of inclusion.

The inclusion criteria are listed in Table 2 and the exclusion criteria in Table 3.

**Table 2 table2:** Inclusion criteria.

Study group	Inclusion criteria
IBD^a^	Males and females aged over 18 years Patients with a confirmed IBD diagnosis Written informed consent obtained
HC^b^	Males and females aged over 18 years Good level of health Written informed consent obtained

^a^IBD: inflammatory bowel disease.

^b^HC: healthy controls.

**Table 3 table3:** Exclusion criteria.

Exclusion criteria		Details

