### Power Calculation, Statistical Model, and Data Analysis

Based on previous studies, the power of the study, with an α of .05 and a power of 80%, the required number of cases and controls is 52 and 26, respectively, for a mean difference in 2 points (SD 3.0) in MOCA scales.

Statistics will be computed using IBM SPSS software version 28.0.1 or newer. Descriptive analysis of the baseline characteristics of the overall population by gender, age, and education will be conducted. Continuous variables will be presented as the mean (SD) or the median (IQR), and countable data will be presented as numbers and percentages. Comparisons of groups will be conducted using the t-test or the Wilcoxon rank-sum test based on the type of distribution of data and the homogeneity of the variance. The chi-square test or the Fisher exact probability method will be used for counting data, as appropriate.

Multiple linear and logistical regression analyses will be performed to evaluate the association between outcomes and potential risk factors identified in the questionnaires. Participants lost to follow-up will be treated as right-censored data. The Pearson coefficient will be used to assess the correlation between cognitive scores and serum levels of the studied biomarkers. A 2-sided significance level of .05 will be used for all primary and secondary analyses unless stated otherwise.

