## Results

The collection of study data started in December 2021, and it is currently ongoing. Since the start of the study, 53 patients with IBD have been recruited and 50 HC were matched until the moment of this paper being published. The blood samples collected were stored according to the laboratory procedures. Data collection should end in January 2030. Intermediary analysis will be performed in April 2024 after the first 50 patients recruited go through the 12-month follow-up visit. Recruitment will continue until the number of participants in the IBD and HC groups is met (n=100 for each group).

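### Controls are matched on age, sex and education, but the stated group tests ignore the matching, so the primary comparison is less precise than the design allows

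*Protocol article*

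**What the plan says.** **Design.** The Methods paragraph of the Abstract plans at least 100 patients "matched with 100 healthy individual controls. The matching will include sex, age, and education". Sites, Population, and Case and Control Definitions repeats it: "The HC will be matched with the patients with IBD based on age, sex, and education". Results shows matching under way: "53 patients with IBD have been recruited and 50 HC were matched". The article does not say whether matching is pair by pair or by frequency.

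**Analysis.** Power Calculation, Statistical Model, and Data Analysis says of continuous outcomes: "Comparisons of groups will be conducted using the t-test or the Wilcoxon rank-sum test based on the type of distribution of data". Homogeneity of variance is the other condition for choosing between the two tests. For categorical outcomes: "The chi-square test or the Fisher exact probability method will be used for counting data, as appropriate". Multiple linear and logistic regressions are planned "to evaluate the association between outcomes and potential risk factors identified in the questionnaires". The significance level is two-sided .05.

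**Status of the comparison.** Table 1 lists cognitive scores in the IBD group against controls as a primary objective.

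**The concern.** The rank-sum, chi-square and Fisher tests are all for independent samples. The t-test stands beside the rank-sum test, not the signed-rank test, and is chosen partly on equality of variances, which matters only for the two-sample form. So it is most naturally read as unpaired. No paired test, matched-set term or adjustment for age, sex and education is stated for the group comparison.

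This matters if the matching factors predict the outcome, and the article expects that they do. The Results paragraph of the Abstract names more education and younger age as possible protection against MCI, and Unexpected Findings links both to better test performance. Scores of matched participants would then be positively correlated, and the difference in means would vary less than an independent-samples standard error says. At stake is the precision that matching was meant to buy: confidence intervals wider than they need be, and an actual test size below .05.

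**Working it through.** **1. The article's own sample size.** Inputs from the power section: difference 2 MOCA points, SD 3.0, two-sided .05, power 80%, 52 cases and 26 controls. For two independent means at 2:1:

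n(controls) = (1 + 1/2) × [3 × (1.960 + 0.842)/2]² = 26.5, and n(cases) = 53.0.

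Rounded up this is 27 and 54, within two of the stated figures. With 26 and 52 the power is 79.3% by the normal approximation and 78.2% by the noncentral t. The stated figure is therefore an independent-samples calculation with no matching in it.

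**2. Standard errors with n matched pairs.** The within-pair correlation ρ is an assumption, taken as 0.1 to 0.5. Under close matching it is roughly the share of score variance that age, sex and education explain.

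- Independent: SD × √(2/n) = 3 × √(2/100) = 0.424
- Paired: SD × √(2(1 − ρ)/n)
- Ratio: 1/√(1 − ρ)
- Actual size of the nominal 5% unpaired test: 2 × [1 − Φ(1.96/√(1 − ρ))]

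| ρ (assumed) | Paired SE, n = 100 | Independent/paired SE | Actual size of unpaired test |
|---|---|---|---|
| 0.1 | 0.402 | 1.05 | 3.9% |
| 0.3 | 0.355 | 1.20 | 1.9% |
| 0.5 | 0.300 | 1.41 | 0.6% |

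A simulation of 20,000 studies of 100 pairs agrees. The independent standard error averaged about 0.424, against an empirical SD of the difference of 0.403, 0.352 and 0.301. The unpaired test rejected a true null in 3.8%, 1.8% and 0.7% of runs, and the paired test in about 5%.

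**3. Power (noncentral t, SD 3).** The 1-point difference is an assumption. The 50+50 first phase is in Plan for Publication and Future Data Collection.

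| Setting | Unpaired formula | Paired, ρ = 0.1 | Paired, ρ = 0.3 | Paired, ρ = 0.5 |
|---|---|---|---|---|
| 2 points, 100 per group | 99.7% | 99.8% | >99.9% | >99.9% |
| 2 points, 50 per group | 91.0% | 93.1% | 97.4% | 99.6% |
| 1 point, 100 per group | 65.0% | 69.2% | 79.7% | 91.0% |

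**4. A refinement.** The unpaired column is the usual formula for unrelated samples. When the unpaired test is applied to matched data, the difference itself varies less, so its power is about Φ((d − t × independent SE)/paired SE).

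- 1 point, 100 per group: the threshold is 1.972 × 0.424 = 0.837. Power is 65.8%, 67.7% and 70.7% at ρ = 0.1, 0.3 and 0.5.
- 2 points, 50 per group: the threshold is 1.984 × 0.600 = 1.191. Power is 92.2%, 94.7% and 97.2%.

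Simulation (40,000 runs per setting) agrees within 0.2 percentage points. The gain from respecting the matching is thus somewhat smaller than the table in step 3 suggests, but in the same direction.

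**The case against.** The strongest reply is that little is lost where the study is aimed. At the article's own 2-point target, the unpaired test has about 99.7% power with 100 per group and 91% with 50 per group. That stands, and it sets the weight of the point.

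Three further objections stand in part.

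- **The correlation is not in the article.** Some features could lower it: age over 70 is a relative exclusion, many conditions that impair cognition are excluded, and MOCA gives an extra point for 12 or fewer years of education. For the biomarkers the article supports no value at all. At ρ = 0 nothing is lost.
- **Individual pairing is not stated.** If matching is by frequency there are no pairs, and paired tests do not apply. An unadjusted standard error is still too large if the factors are prognostic, and covariate adjustment is the remedy.
- **The regressions might recover the precision.** Education is collected (Table 6), and the demographic variables are meant for stratifying participants. A regression with group, age, sex and education would answer the point, but the article describes the regressions only for questionnaire risk factors.

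A reader might go further and infer that the comparison is biased or produces false positives. The article does not support that. The groups are defined by having IBD or not and cognition is the outcome, so ignoring the matching costs precision without shifting the mean difference. Nor does the absence of a matching tolerance count against the plan, since an article may leave that detail to the full protocol.

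**Conclusion.** The mismatch is real: the design matches on three factors, and the stated primary group comparison uses none of them. If the factors predict cognitive score, the standard error is 5% to 41% too large for assumed correlations of 0.1 to 0.5, and the nominal 5% test has an actual size of 3.9% down to 0.6%. The direction rests on the article's own expectation about age and education. The size rests on an assumed correlation and on SD 3.0.

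It would be wrong to conclude that the study is underpowered for its planned 2-point difference. The cost lies in interval width, in differences smaller than planned, and to a lesser degree in the first phase. It is an efficiency correction of modest weight, worth making because it is nearly free.

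**What to change.** State whether matching is individual or by frequency. Make the primary comparison of cognitive scores and biomarkers a linear regression on group with age, sex and education as covariates, and use logistic regression with the same terms for MCI yes/no. This is valid under either form of matching and keeps patients without a matched control (53 − 50 = 3 at the time of the article).

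If matching is individual, store the pair identifier and add a matched-set effect. Alternatively, use the paired t-test or signed-rank test for scores, and McNemar's test or conditional logistic regression for MCI. Hospital need not be a covariate: the article does not say how cases and controls divide between the two hospitals.

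The cost is a few sentences in the analysis section and, for individual matching, one extra variable in the database. No new measurements are needed, and because recruitment is continuing, pair links can still be recorded as controls are enrolled.

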## Abstract

**Background:**

Mild cognitive impairment (MCI) and Alzheimer’s disease (AD) might be more frequent in patients with inflammatory bowel disease (IBD), but the relationship between these 2 entities is yet to be entirely established. Certain blood biomarkers (eg, serum amyloid A [SAA] and serum homocysteine [Hcy], which increase in IBD and MCI; brain-derived neurotrophic factor [BDNF], which decreases in MCI and AD but is not clearly modified in IBD; and S100 calcium-binding protein B [S100B], which increases in the blood-brain barrier and neuronal lesions) might predict the stage of MCI or dementia or progression to a further state. The gut–brain axis (GBA) might be the key to the development of MCI in patients with IBD, along with systemic inflammation and the possible and unknown adverse effects of disease-modifying medication.

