**Results:**

Data collection started in December 2021 and is ongoing. So far, 53 patients with IBD have been recruited and 50 HC matched. Data collection should end in January 2030. Intermediary analysis will be performed in April 2024. We expect patients with IBD to have lower scores on cognitive testing and a positive correlation between disease length and cognitive impairment level. In addition, the levels of stress, anxiety, and depression should be higher in the IBD group. The serum levels of the 4 biomarkers could correlate or anticorrelate with cognitive scores and serve as predictive factors for MCI or dementia development. A higher level of education, a younger age, the absence of malabsorption, and good disease control might serve as protectors against MCI.

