The TMT involves the subject drawing a trail between 2 points, with the entire operation being timed. It has 2 different parts, TMT-A and TMT-B. TMT-A involves drawing a continuous line between numbers. TMT-B involves drawing a continuous line, alternating letters and numbers. An example of the test is provided before each part. TMT-A has a maximum time of 100 seconds, and 101 seconds means the subject has failed the test. TMT-B has a maximum time of 300 seconds, and 301 seconds means the subject has failed the test.

The Digit Symbol Substitution Test (DSST) involves the subject changing some numbers to symbols as specified in the legend of the test. A training zone is first created. If the training is completed, the subject is given 90 seconds to complete as many substitutions as possible. Correct and incorrect answers are counted.

In forward digit span testing (FDST) and backward digit span testing (BDST), the subject must recall the numbers provided by the examiner in forward order and then in backward order. FDST involves strings of numbers ranging from 2 to 8 numbers, and BDST involves strings of numbers ranging from 2 numbers to 7 numbers. Each string has 2 different variants, and the subject must make a maximum of 1 mistake in these variants, otherwise the test ends.

The Depression-Anxiety-Stress Scale (DASS) is a scale that includes 21 questions split into 3 categories (depression, stress, and anxiety), with 7 questions per category, the questions being interleaved. Each question has a score from 0 to 3, and the result is multiplied by 2.

The Harvey-Bradshaw Index (HBI) and the Simple Clinical Colitis Activity Index (SCCAI) are used for screening the subject. In this study, they are part of the inclusion criteria.

The quality-of-life instruments available in Romania are limited; therefore, the World Health Organization Quality of Life Brief Version (WHOQOL-BREF) will be used in order to determine the quality of life of our participants. The Instrumental Activities of Daily Living (IADL) is an 8-item scale that includes some instrumental daily activities, and it is a useful and essential tool for differentiating MCI from dementia. The Katzl ADL scale is a 6-item scale that includes casual daily activities and is also a useful and essential tool for differentiating MCI from dementia.

A blood sample will be obtained from each participant.

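### The primary biomarker–cognition association is fixed as an unadjusted Pearson coefficient: no age adjustment, no distribution rule, and no statement on whether the two groups are combined

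*Protocol article*

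**What the plan says.** The section Power Calculation, Statistical Model, and Data Analysis gives one sentence to this analysis: "The Pearson coefficient will be used to assess the correlation between cognitive scores and serum levels of the studied biomarkers". Table 1 lists the association among the primary objectives, and the Discussion summary names it as the aim, with TMT-A and TMT-B among the scores to be correlated.

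Three neighbouring statements define what that sentence does not cover:

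- The choice between a parametric and a rank method according to distribution is stated for group comparisons only.
- Multiple regression is planned "to evaluate the association between outcomes and potential risk factors identified in the questionnaires". The four serum markers come from ELISA, not from a questionnaire, so on its wording this sentence does not cover them.
- "A 2-sided significance level of .05 will be used for all primary and secondary analyses unless stated otherwise".

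On the inputs, the Abstract describes SAA and Hcy as markers "which increase in IBD and MCI" and expects lower cognitive scores in IBD. Controls are matched on age, sex and education. Adults over 18 are eligible, and age over 70 is only a relative exclusion. For the Trail Making Test, "TMT-B has a maximum time of 300 seconds, and 301 seconds means the subject has failed the test"; TMT-A has the corresponding code of 101 seconds.

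**The concern.** A raw Pearson coefficient answers the question only if nothing else drives both variables and if their relation is roughly linear without dominant extreme values. The protocol itself gives reasons to doubt the first condition. It names age as a risk factor for MCI and a younger age as protective. Matching makes the age distributions of the two groups alike, but it leaves the spread of age inside each group untouched. Any marker that also changes with age will therefore correlate with cognition through age alone.

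The second gap is that the sentence does not say whether one coefficient is computed across all participants or one per group. The protocol expects IBD patients to differ from controls in both SAA or Hcy and cognition, so a pooled coefficient would partly restate the group difference.

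The third is that the distribution rule applied to group comparisons is not carried over to the correlation, where skewed markers and coded test times would matter just as much.

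At stake is the article's main translational claim, that cheap serum markers may predict MCI. The stated method could support it without any marker-specific link, or could miss a real monotone link.

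**Working it through.** **The plan's own figure.** The protocol states that "the required number of cases and controls is 52 and 26, respectively, for a mean difference in 2 points (SD 3.0) in MOCA scales", with two-sided alpha .05 and 80% power. At a 2:1 ratio, controls = (1 + 1/2) × (1.960 + 0.842)² × 3² / 2² = 1.5 × 7.849 × 2.25 = 26.49, and cases = 52.98. Rounding up gives 27 and 54. The stated 26 and 52 give 79% power by the normal approximation, so the figure reproduces to within rounding. It concerns the MOCA difference only; the article gives no figure for the correlation. It does supply a standardised cognitive difference of 2/3.0 = 0.667, used below. The recruitment target is 100 per group.

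**Age.** If age correlates a with the marker and a with the score (absolute values, assumed) and there is no direct link, the induced correlation is a × a. The rejection rate comes from Fisher's z: the expected statistic is atanh(r) × √(n − 3), set against 1.96.

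| a | r | p<.05, n=100 | p<.05, n=200 |
|---|---|---|---|
| 0.2 | 0.04 | 7% | 9% |
| 0.3 | 0.09 | 14% | 24.5% |
| 0.4 | 0.16 | 36% | 62% |

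Example: atanh(0.16) × √97 = 0.1614 × 9.849 = 1.59, and P(Z > 1.96 − 1.59) = 36%. Adjusting for age returns the rate to 5%.

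**Pooling, if it were done.** With zero correlation inside each group and equal group sizes, r = 0.25·d₁·d₂ / √[(1 + 0.25·d₁²)(1 + 0.25·d₂²)], with d₁ = 0.667 from the protocol and d₂ the marker difference in SD units (assumed).

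| d₂ | r | p<.05, n=200 |
|---|---|---|
| 0.3 | 0.05 | 10% |
| 0.5 | 0.08 | 19% |
| 0.8 | 0.12 | 38% |
| 1.0 | 0.14 | 52% |

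Example for d₂ = 1: 0.1667 / √(1.111 × 1.25) = 0.1667 / 1.1785 = 0.141. A group term returns the rate to 5%.

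**Skew.** Assume a lognormal marker with log-SD s and a latent correlation of 0.3. The population Pearson r is 0.3·s / √(exp(s²) − 1). Power was simulated at n=100.

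| s | Pearson r | Pearson, raw | Spearman | Pearson, log marker |
|---|---|---|---|---|
| 0.5 | 0.28 | 83% | 84% | 86% |
| 1.0 | 0.23 | 69% | 81% | 85% |
| 1.5 | 0.15 | 55% | 83% | 87% |

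At a log-SD of 0.3, Pearson has 85% and Spearman 82%, so with mild skew nothing is lost.

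**Fail codes.** In the same simulation, capping 2% to 15% of times lowered Pearson power by about 2 points or less for log-SD up to 1.0. Only strong skew with many failures cost more: in a check at log-SD 1.5 with 15% failing, power fell from 53% to 47%.

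**The case against.** The article condenses a fuller plan, and a statistical analysis plan may add detail. That excuses silence. Here, however, the method is named, and a later plan would have to depart from this sentence rather than fill a gap.

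Several stronger readings are tempting, and the document does not support them:

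- **That the plan pools the groups.** It never says so. Table 1 and the Discussion summary set the association in IBD against controls, which fits one coefficient per group at least as well. The 10% to 52% range is therefore conditional. The Abstract also says BDNF is not clearly modified in IBD, so no group shift can be presumed for that marker.
- **That disease duration suffers the same fault.** The article expects "a positive correlation between disease length and cognitive impairment level", but the Pearson sentence covers serum markers only. No method is fixed for duration.
- **That the markers are known to be skewed.** No distribution is given. SAA is described as an acute-phase protein, but testing is postponed until flares are over, which may limit extreme values.
- **That the fail codes seriously damage the analysis.** They would enter as measured seconds because no other handling is stated. Their cost in power is generally small, and the exclusion of stroke, dementia and other neurological and psychiatric disease makes frequent failure unlikely.

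One more objection stands. Inflammation and mood are among the pathways the study proposes, so adjusting the primary association for C-reactive protein or DASS-21 could remove the effect of interest. What none of these objections removes is the missing age adjustment, the unstated role of group and the missing distribution rule.

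**Conclusion.** The point holds in this limited form and should be fixed. The age problem is the firmest part, because it arises whether the groups are combined or kept apart: induced r of 0.09 to 0.16, significant in 14% to 36% of analyses at n=100 instead of 5%, on assumed age correlations of 0.3 to 0.4. At 0.2 the rate is only 7%. The pooling figures apply only if the groups are pooled and rest on an assumed marker difference. The loss of power rests on an assumed log-SD and runs from none to nearly 30 percentage points (83% against 55%). The Trail Making codes are a minor matter of correct handling. The MOCA group comparison and its sample size are unaffected, and the fault can be corrected at analysis without new data.

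**What to change.** Replace the Pearson sentence with a specification along these lines:

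- Estimate the association separately within IBD and within controls, or in one model with a group term if they are combined.
- Adjust for age, sex and education.
- Use partial Spearman correlation, or regression on log-transformed markers.
- Rank TMT-A and TMT-B failures as worst, or treat them as right-censored at 100 and 300 seconds, rather than as 101 and 301 measured seconds.
- Keep C-reactive protein and DASS-21 for sensitivity models. Both may lie on the causal path, and C-reactive protein is taken from hospital registry values that may not exist for every control.

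The cost is a change of wording. Age, sex and education are the matching variables and so must already be recorded. The price in power when a marker is not skewed is small (82% for Spearman against 85% for Pearson at log-SD 0.3). The amendment should be dated before the biomarker results are analysed.

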“Stress disorder” is a term used to describe a mental health condition that can develop in response to a traumatic or stressful event. Individuals may experience a range of symptoms, including intrusive thoughts or memories of the traumatic event; nightmares; and avoidance of people, places, or activities that are associated with the trauma. They may also experience physical symptoms, such as a racing heart, sweating, and muscle tension [14]. “Anxiety disorder” is a general term that refers to a group of mental health conditions characterized by excessive and persistent feelings of worry, fear, and unease [15]. Depression is a mental health condition characterized by persistent feelings of sadness, hopelessness, and a loss of interest in activities that were once enjoyable. It is a common and serious condition that can have a significant impact on an individual’s daily life and overall well-being. In addition to feelings of sadness, depression can also cause a range of physical and emotional symptoms, including fatigue, changes in appetite and sleep patterns, difficulty in concentrating, and thoughts of self-harm or suicide. The exact cause of depression is not fully understood, but it is believed to be related to a combination of genetic, biological, environmental, and psychological factors [16-18].

Homocysteine (Hcy) is an amino acid. Studies have shown that individuals with IBD have higher serum concentrations of Hcy compared to healthy controls (HC). The exact reason for this association is not fully understood, but it may be related to nutrient deficiencies caused by the inflammation and malabsorption in the gut that often occur in IBD. There is evidence to suggest that elevated levels of Hcy in the blood are associated with an increased risk of MCI and dementia. High Hcy levels have been linked to damage of the blood vessels in the brain, leading to decreased blood flow and oxidative stress, both of which can contribute to cognitive decline [19-23].

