## Discussion

### Summary

The aim of the study is to evaluate whether there is a correlation between the level of the blood biomarkers studied (SAA, Hcy, S100B, and BDNF) and cognitive scores (MOCA, MIS, FDST, BDST, TMT-A, TMT-B, DSST) in a period of 12-48 months in patients with IBD compared to HC. Previous studies have shown that patients with IBD have lower cognitive scores compared to HC [3,5,8,9,11,12,35]. We expect similar results. Multiple biomarkers have been found modified in patients with MCI but also in patients with IBD; therefore, some reliable biomarkers have been selected for analysis [19-34]. A positive correlation between worse cognitive scores and elevated serum levels is expected to be found.

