### Perspectives and Clinical Implications

This study might serve as another “brick in the wall” for the question of whether the GBA is involved in the development of MCI. If the results show a correlation between the clinical onset and length of IBD and the risk of MCI development, we could rethink treatment strategies. Serum biomarkers could prove a useful tool for stratifying the risk of MCI development, as their levels can be determined for all patients and the costs are not high.

A possible link between IBD and MCI through the GBA should be further investigated at the molecular level in order to find the underlying pathogenic mechanism. According to the diagnosis criteria of AD, if we find a progression from MCI to AD in patients with IBD, perhaps a clinical study involving the detection of abnormal proteins in the cephalorahidian fluid obtained from a lumbar puncture could be performed in the future. In addition, we could expect some clinical trials involving prevention of the progression from MCI to AD if some more underlying pathogenic mechanisms are found. Furthermore, clinical trials studying the possible prophylactic treatments for the development of MCI must be performed in order to stop this invalidating disease from affecting the population.

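### The biomarker–cognition objective is tested only by unadjusted Pearson coefficients, so age, education and, if the groups are pooled, IBD status can produce the correlation

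*Protocol article*

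**What the plan says.** The section Power Calculation, Statistical Model, and Data Analysis states: "The Pearson coefficient will be used to assess the correlation between cognitive scores and serum levels of the studied biomarkers". It does not say whether the coefficient is computed across all participants or within each group. The multiple linear and logistic regressions in the same paragraph are there to evaluate "the association between outcomes and potential risk factors identified in the questionnaires". Serum markers are not questionnaire items.

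Table 1 lists the association of the four markers with cognitive scores, set against healthy controls, among the primary objectives. The Aim section intends the markers as predictors of MCI or dementia, and Perspectives and Clinical Implications adds: "Serum biomarkers could prove a useful tool for stratifying the risk of MCI development".

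The protocol itself treats several other factors as related to cognition or to the markers:

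- **Age and education.** The Abstract (Results) says: "A higher level of education, a younger age, the absence of malabsorption, and good disease control might serve as protectors against MCI".
- **IBD and cognition.** The Discussion summary says: "Previous studies have shown that patients with IBD have lower cognitive scores compared to HC".
- **IBD and the markers.** The Background says: "Studies have shown that individuals with IBD have higher serum concentrations of Hcy compared to healthy controls (HC"). The Abstract says that SAA rises in IBD, and the Background says that S100B is raised. For BDNF the Abstract reports no clear change in IBD.

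**The concern.** A crude correlation between a marker and a test score mixes any direct relation with whatever the two share. Matching on age, sex and education makes the two groups alike on average. It does not make participants alike, and they range from over 18 to about 70 years (older age is only a relative exclusion) with any amount of schooling. If a marker varies with age or education, and the score does too, the coefficient is non-zero even where the marker adds nothing.

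Pooling adds a second route. If IBD raises a marker and lowers the scores, combining the groups creates a correlation that is absent within either group. On the protocol's own premises this applies to SAA, Hcy and S100B.

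At stake is a primary objective and the proposed use of the markers to grade risk. A significant coefficient could say no more than that a participant is older, less educated or has IBD. The plan to publish a first phase of 50 patients and 50 controls means that such coefficients could appear in print early.

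**Working it through.** **The plan's own figure first.** The protocol says "with an α of .05 and a power of 80%, the required number of cases and controls is 52 and 26, respectively". The effect behind it is a MOCA gap of 2 with an SD of 3.0. With a 2:1 ratio and a two-sided test:

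controls = (1 + 1/2) × [3.0 × (1.960 + 0.842) / 2]² = 26.49; cases = 2 × 26.49 = 52.98.

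The stated 26 and 52 agree with this to within rounding (power at 26 and 52 is 79.3% by the normal approximation). The inputs can therefore be reused: the standardised MOCA gap is d1 = 2/3.0 = 0.667.

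**Inputs from the protocol.** 100 + 100 participants; two-sided .05; d1 = 0.667; 4 markers × 7 scores = 28 coefficients. All rates below are for one coefficient.

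**Inputs assumed, shown as ranges.** The shift of the marker between groups (d2, in SD), and the correlations of age or education with the score (a) and with the marker (b). The protocol gives none of these.

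**Null considered throughout.** No relation between marker and score once group and age (or education) are held fixed. A valid test of that null rejects 5% of the time.

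**Rejection probability.** By Fisher z: 1 − Φ(1.96 − m) + Φ(−1.96 − m), with m = atanh(|r|) × √(n − 3).

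**Route 1: IBD status alone, equal groups pooled.** |r| = d1·d2 / √[(d1² + 4)(d2² + 4)].

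For d2 = 1.0: 0.667 / √(4.444 × 5) = 0.141. Then m = 0.142 × 14.04 = 2.00 and the probability is 0.515.

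| Marker shift d2 (SD) | Induced absolute r | Rejects, n=200 | Rejects, n=100 (50+50) |
|---|---|---|---|
| 0 | 0 | 5% | 5% |
| 0.3 | 0.047 | 10% | 7.5% |
| 0.5 | 0.077 | 19% | 12% |
| 0.8 | 0.117 | 38% | 21% |
| 1.0 | 0.141 | 52% | 29% |

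**Route 2: age or education alone.** |r| = a × b. This applies whether or not the groups are pooled.

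| a × b | Induced absolute r | Rejects, n=200 | Rejects, n=100 |
|---|---|---|---|
| 0.3 × 0.1 | 0.03 | 7% | 6% |
| 0.3 × 0.3 | 0.09 | 25% | 14% |
| 0.4 × 0.4 | 0.16 | 62% | 36% |

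**Both routes, by simulation (4,000 runs, 100 per group).** The last column is the partial correlation given group and age.

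| d2; a × b | Pooled Pearson | Pearson within IBD only | Pooled, adjusted |
|---|---|---|---|
| 0.3; 0.3 × 0.1 | 18% | 6% | 4.9% |
| 0.5; 0.3 × 0.2 | 47% | 9% | 4.9% |
| 0.8; 0.3 × 0.3 | 81% | 15% | 5.0% |
| 1.0; 0.4 × 0.3 | 94% | 22% | 4.7% |

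Across all simulated scenarios, including those with one route or none, the adjusted test rejected in 4.7% to 5.4% of runs.

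**The case against.** **The inflation rests on assumed figures.** This stands. The protocol says nothing about how the markers vary with age or education, and gives no size for any difference between groups. With a zero marker shift and no age or education link, the rate is the nominal 5%.

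**Pooling is not stated.** This also stands. Both Table 1 and the Discussion summary speak of a comparison with controls, which can be read as one coefficient per group. The IBD route then disappears and the combined scenarios fall to between 6% and 22%. Age and education remain. For BDNF the IBD route is not established in any case, and the Background calls the evidence on SAA in IBD limited.

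**Shared causes are already reduced.** In part. The MOCA education point, the relative exclusion above 70 years, and the exclusions for stroke, diabetes, hypothyroidism and vitamin supplements narrow them. They do not remove age or education from the coefficient.

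**Pearson answers the marginal question at its nominal level.** True for the bare question of whether a correlation exists. The Aim goes further and wants the markers as predictive factors, which needs information beyond age, education and diagnosis.

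**A condensed article leaves covariates to the full plan.** A missing covariate list would be no finding. Here the article names a method for this objective and assigns its regressions elsewhere. The Abstract does call the markers laboratory outcomes, so they might enter the regressions as dependent variables, but that still gives no adjusted relation between marker and cognition.

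**Conclusion.** The point holds in conditional form. The only method named for this primary objective is unadjusted, and matching does not repair that. Age or education can produce the correlation under either reading of the plan, and IBD status can do so if the groups are pooled.

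For one coefficient, the rejection rate with no conditional link is about 10% to 52% from IBD status alone (pooled n=200, marker shift 0.3 to 1.0 SD). From age or education alone it is about 7% to 62% at n=200, or 6% to 36% in one group of 100 (0.3 × 0.1 to 0.4 × 0.4). From both, pooled, it is about 18% to 94%. These ranges rest on assumed marker shifts and correlations; only the MOCA gap comes from the protocol.

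A reader might infer that a significant correlation is to be expected even if no marker relates to cognition. The documents do not support that. The rate passes one half only under strong assumed confounding, such as a shift of about 1 SD, a correlation product of about 0.15 at n=200, or a sizeable mix of the two. Nor do they support saying that IBD status is in the coefficient for certain, or for all four markers.

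**What to change.** In the statistical section:

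1. State whether the biomarker–cognition analysis is pooled or done within each group.
2. Regress each cognitive score on each marker (or use a partial correlation), adjusted for age, sex and years of education, and for IBD/control group if pooled.
3. Keep the Pearson coefficient as a descriptive figure.
4. Base any statement about risk stratification on the gain over age, sex and education, such as the change in R² or in AUC.

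The change is one of wording. Age, sex and education are already recorded for matching, with education in years in Table 6. At n=200 the pooled model has 194 residual degrees of freedom (200 − 6) against 198 for Pearson, a trivial loss. The downside is that reported associations will usually be smaller. The wording should be settled before the first-phase results are analysed.
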